### **Intent-to-treat (ITT) efficacy population:**

This population will consist of the entire population for whom any aspect of treatment with Metvix® cream was initiated. This population will be analyzed using the last observation carried forward (LOCF) method to impute missing values and to avoid possible bias introduced by non-random dropout of patients. A lesion with missing response at 3-months, will be handled as non-complete response in the calculation of the patient response rate.

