## 5.6 Follow Up Evaluation

### 5.6.1 Efficacy follow-up

Treatment response will be assessed at the follow-up visits; 3, 12 and 36 months after treatment. The localization of the treatment sites will be made from the body chart made and the photos taken at baseline.

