### **8.2.1 Disposition of Lesions**

The number of lesions which are included into the study, which receive Metvix® cream, which are included in safety and/or efficacy evaluation, and which complete each phase of the study, as well as withdrawals will be summarized using counts and percentages of lesions.

Each lesion will be identified, randomized, treated and followed up individually. Patient identification will be recorded anonymously, to account for potential individual susceptibility with respect to response.

The primary outcome is defined as “cure” or “no cure” of a lesion at 3 years, i.e. a binary variable. From previous experience it is expected that the reference treatment leads to a probability of cure of 80 %.

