### **Per-protocol (PP) efficacy population**

This population will consist of all treated BCC-lesions, except lesions considered not evaluable due to major deviations from the protocol. Major deviations may include: inclusion criteria not respected, non-available efficacy assessment, visit window discrepancy, or discrepancies from the treatment schedule. Major deviations will be assessed before start of the statistical analyses. Only observed data will be part of the per-protocol analysis. A lesion with missing response at 3-months will be excluded from the calculation of the patient response rate.

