### **8.2.2 Efficacy**

The primary endpoint will be lesion response rate determined by clinical assessment (visual inspection and palpation) 3, 12 and 36 months after Metvix® PDT treatment. Lesion response rate is defined as number of lesions in complete response at the follow-up.

The primary hypothesis to be tested will be:

$$H_0: \mu_1 \leq \mu_2 - \delta_0 \text{ vs. } H_A: \mu_1 > \mu_2 - \delta_0$$

Here  $\mu_1$  = expected response rate for treatment regimen 1,  $\mu_2$  = expected response rate for treatment regimen 2,  $\delta_0 = 0.1$ , non-inferiority margin.

As one patient may yield more than one lesion, a mixed effects logistic regression model with patient identity as random factor will be considered. Different lesions within the same patient will be subject to stratified randomization.

A two-sided 95% confidence interval for difference in lesion response rate will be calculated and supplemented by odds ratio from the logistic regression. The calculation of the confidence interval will be based on data pooled across centers.

Efficacy results will be presented for the ITT and for the PP population.

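### Carrying the last observation forward in the ITT set counts every lesion lost after a complete response as cured at 3 years, which can favour non-inferiority when regime 1 fails late

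*Protocol*

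**What the plan says.** Protocol section 8.2.1 fixes the outcome: "The primary outcome is defined as “cure” or “no cure” of a lesion at 3 years". Section 5.6.1 fixes the visits: "Treatment response will be assessed at the follow-up visits; 3, 12 and 36 months after treatment". The follow-up table in section 5.6.2 schedules only lesions in complete response for the 12- and 36-month visits.

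The paragraph on the ITT efficacy population then says: "This population will be analyzed using the last observation carried forward (LOCF) method to impute missing values", with the purpose "to avoid possible bias introduced by non-random dropout of patients". It adds one specific rule: "A lesion with missing response at 3-months, will be handled as non-complete response in the calculation of the patient response rate".

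The per-protocol paragraph takes a different line: "Only observed data will be part of the per-protocol analysis". Section 8.2.2 sets a non-inferiority test with margin 0.10 and a two-sided 95% interval for the difference in lesion response rate, and says "Efficacy results will be presented for the ITT and for the PP population". It does not say which set decides, or that both must agree.

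**The concern.** Recurrence accumulates over three years, and once a lesion has relapsed it cannot return to being cured at 36 months. Carrying a 3- or 12-month complete response forward therefore assumes that no lost lesion relapses later. That assumption creates a bias; it does not remove one.

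Because only lesions in complete response are scheduled beyond the 3-month check, the value carried forward for a lesion lost in later follow-up will usually be a complete response. Section 1.2 also withdraws patients, not lesions, for non-complete response. A second lesion in complete response in the same patient might then leave follow-up and be carried as cured. This last effect is not quantified here.

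In a non-inferiority trial, hiding late failures in both arms can bring a true deficit closer to zero and make a false claim for the simplified regime more likely.

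**Working it through.** **Inputs from the protocol.** Margin 0.10 and two-sided 95% interval (section 8.2.2). Reference cure 85%, 170 lesions required and 187 recruited per group (section 8.3).

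**The plan's own figures.** An exact score test with 170 per group has power 81.3% at one-sided 5% and 85% cure, so the 170 reproduces on that reading. The allowance for loss is (187 − 170)/187 = 17/187 = 9.1%.

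**Assumptions not in the protocol.** True 3-year cure is p1 = 75% for regime 1 and p2 = 85% for regime 2, a deficit exactly at the margin. Lesions are independent. A share L of lesions in early complete response is lost before any relapse is seen, unrelated to later relapse. The split between early and late failures is varied.

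**Formula.** Let f be the share of an arm's lesions that fail after an early complete response. The cure rate under the carry-forward rule is p + L × f. With equal loss the expected difference is (p1 − p2) + L × (f1 − f2).

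*All failures late, L = 17/187:*
- regime 1: 0.75 + 0.0909 × 0.25 = 0.7727
- regime 2: 0.85 + 0.0909 × 0.15 = 0.8636
- difference: −0.0909

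*Half of failures late, L = 17/187:*
- regime 1: 0.75 + 0.0909 × 0.125 = 0.7614
- regime 2: 0.85 + 0.0909 × 0.075 = 0.8568
- difference: −0.0955 (from unrounded rates)

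**Error rate.** This is the probability that the Wald 95% lower limit exceeds −0.10, by enumeration of both binomials with 187 per arm.

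| Pattern of failure | Difference at 9.1% loss | Error at 9.1% | Difference at 20% loss | Error at 20% |
|---|---|---|---|---|
| All failures late (f 25% vs 15%) | −9.1 points | 4.4% | −8.0 | 8.0% |
| Half late (f 12.5% vs 7.5%) | −9.5 | 3.4% | −9.0 | 4.6% |
| Whole deficit early (early response 85% vs 95%; f 10% vs 10%) | −10.0 | 2.6% | −10.0 | 2.6% |
| Early gap larger than 3-year gap (80% vs 95%; f 5% vs 10%) | −10.5 | 2.0% | −11.0 | 1.4% |

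With no loss the error is 2.6%. With observed outcomes on 170 per arm after random loss it is also 2.6%, so the inflation comes from the carry-forward rule and not from the loss.

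**Hand check of the first row.** The standard error is √[(0.7727 × 0.2273 + 0.8636 × 0.1364)/187] = 0.0396. The shift is (0.1000 − 0.0909)/0.0396 = 0.23. The upper tail beyond 1.96 − 0.23 = 1.73 is about 4.2%, close to the enumerated 4.4%.

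**Unequal loss, all failures late.**
- 15% lost in regime 1 and 5% in regime 2: difference −7.0 points, error 11.9%.
- 5% and 15%: difference −11.0 points, error 1.4%.

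**The other reference rate.** The synopsis and section 8.2.1 give 80%. With 70% against 80% and early response of 95% in both arms, the error is 4.1% at 9.1% loss and 7.0% at 20%.

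**Would scoring all missing lesions as failures be enough?** At 9.1% loss the rates are 0.75 × 0.9091 = 0.6818 and 0.85 × 0.9091 = 0.7727. The difference is again −9.1 points and the error 4.0%, so that rule is no substitute.

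**The case against.** The strongest reply is that the direction is not fixed. Regime 1 starts with one session and a 3-month check, so its excess failures may well appear early. A regime 1 lesion in non-complete response at 3 months that is re-treated and then lost is carried forward as a failure, which counts against regime 1. A relapse already seen at 12 months is carried forward as a failure too. This stands: a reader might infer that the rule always favours non-inferiority, but the third and fourth rows of the table show otherwise.

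The protocol also has an observed-data per-protocol analysis, so the carry-forward result is not the only one presented. That too stands, but only in part. The per-protocol analysis is unbiased only if loss is random, and nothing requires it to agree with the ITT result.

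A reader might further infer that single imputation makes the interval too narrow and so adds a second source of false claims. The figures do not support this. In simulation under the same model (9.1% loss, all failures late), the mean estimated standard error was 0.0395 against an actual spread of 0.0396, with 94.9% coverage of the carry-forward difference. The inflation is bias in the difference itself.

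Finally, the rule for a missing 3-month response might look disposable, because it refers to a rate per patient that no endpoint section defines. It is, however, the only ITT rule for lesions with no post-treatment observation, and section 8.2.2 lists 3 months among the assessment times. It needs rewording, not deletion.

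**Conclusion.** The point holds in conditional form and should be fixed. The protocol's reason for carrying observations forward is wrong for a 3-year cure endpoint, because relapse after loss can never be counted.

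The rule favours non-inferiority when part of any regime 1 deficit arises as relapse after early complete response and loss is similar in the arms or higher in regime 1. At the plan's implied 9% loss the inflation is moderate: from about 2.6% to between 3.4% and 4.4%. The range of 4.6% to 8.0% needs 20% loss, which the protocol does not state. All failures being late is an extreme case. The inflation vanishes if the whole deficit is visible at the 3-month check. It reverses if the early gap exceeds the 3-year gap or if loss is clearly higher in regime 2.

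These figures assume independent lesions and loss unrelated to later relapse. An error rate that depends this much on unplanned dropout is itself a reason to change the rule.

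**What to change.** In the ITT paragraph of section 8.2.1:

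- Replace carry-forward for the 36-month outcome by multiple imputation within regime, conditional on last observed status (in complete response at 3 or at 12 months). An interval-censored estimate of 36-month cure is an alternative.
- Carry forward only observed failures.
- Remove the statement that the method avoids dropout bias.
- Add a sensitivity analysis that scores lost regime 1 lesions progressively worse until the conclusion changes.
- Keep the rule for a missing 3-month response, reword it to the lesion response rate, and state how it fits with the imputation.

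Under missing-at-random, either method aims to preserve the true difference and the nominal error rate. The details of the imputation model can be left to the statistical analysis plan. The cost is protocol wording, some analysis work and a slightly wider interval; no further patients or visits are needed.

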### **8.2.2 Efficacy**

The primary endpoint will be lesion response rate determined by clinical assessment (visual inspection and palpation) 3, 12 and 36 months after Metvix® PDT treatment. Lesion response rate is defined as number of lesions in complete response at the follow-up.

The primary hypothesis to be tested will be:

$$H_0: \mu_1 \leq \mu_2 - \delta_0 \text{ vs. } H_A: \mu_1 > \mu_2 - \delta_0$$

Here  $\mu_1$  = expected response rate for treatment regimen 1,  $\mu_2$  = expected response rate for treatment regimen 2,  $\delta_0 = 0.1$ , non-inferiority margin.

As one patient may yield more than one lesion, a mixed effects logistic regression model with patient identity as random factor will be considered. Different lesions within the same patient will be subject to stratified randomization.

A two-sided 95% confidence interval for difference in lesion response rate will be calculated and supplemented by odds ratio from the logistic regression. The calculation of the confidence interval will be based on data pooled across centers.

Efficacy results will be presented for the ITT and for the PP population.

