**Procedure** Lesion mapping will take place before treatment and at the preset follow-up visits by recording the number and location of the lesions in the CRF. Registration of the lesion clinical extent, location, thickness and subtype will be done at baseline and marked on a form and/ or photographed for later identification. In order to facilitate access of the Metvix® cream and light to all parts of the lesion, the surface of BCC lesions with 5 mm of the surrounding tissue of normal appearance should be prepared using a small dermal curette. The curettage should be performed by scraping in a checked pattern for optimal removal of scales and crusts, and to roughen the surface of the lesion. Thicker lesions require debulking. Metvix® cream will then be applied in a 1.0 mm thick layer to the whole treatment field and then covered using a dressing to avoid any ambient light exposure. Metvix® is applied for 3 hours before the dressing and remnants of cream are removed. Anaesthesia using subcutaneous infiltration anaesthesia without adrenaline will be given individually at the discretion of the investigator. The treatment area is then illuminated using Aktelite CL 128

(Photocure ASA) as a light source; peak wavelength around 631 nm (redlight) and light dose 37 J/cm^2 and exposure time 7-9 minutes. After light treatment each lesion will be randomized to one or two possible treatment regimes; a single MAL-PDT treatment session with re-treatment if there is a non-complete response after 3 months (regimen 1), or two treatment sessions separated by one week (regimen 2).

Two independent pathologists will examine the HES stained diagnostic punch biopsies. Tumour thickness and subtype will be recorded. Various immunohistochemical stains will be used to evaluate their utility for enhanced detection of residual tumours.

**Endpoints** The primary endpoint will be lesions response rate and cosmetic outcome determined by clinical assessment (visual inspection and palpation) 1 and 3 years after Metvix® PDT treatment. Clinically suspected recurrences will be examined by histology. We will report the number of lesion in need of a re-treatment 3 months following the first treatment session in regime 1. Further, report on number and time of lesion to relapse by either regime, 1 or 3 years after PDT and report on adverse events in a period of up to 3 months following last treatment session.

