## Statistics

Simple tabulation as well as logistic regression with lesion recurrence (yes/no, a binary variable) at 3 years will be employed to analyze the outcome. As one patient may yield more than one lesion, a mixed effects model with patient identity as random factor will be considered. Different lesions within the same patient will be subject to stratified randomization. The expected cure rate at 3 years (reference) is set to 80 %. The study aims to detect an experimental success rate of no less than 70 % (the non-inferiority margin 10 %). With a sample size of 170 lesions per group, a difference between the two treatment regime groups of at least 10% can be found with a significance level of 5% and a power of 80%.

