## **3. INVESTIGATIONAL TRIAL DESIGN**

### **3.1 Study Endpoint(s)**

The primary endpoint will be lesions cure rate and cosmetic outcome by treatment regime 1 compared to lesions cure rate by treatment regime 2, assessed 36 months after PDT. The number of lesion in need of a re-treatment 3 months following the first treatment session in regime 1 will be reported. Clinical suspected recurrences are confirmed by histology. Lesion response rate is defined as number of lesions in complete response at 12 and 36 months of follow-up. We will report on adverse events occurring in relation to both treatment regimes from start of treatment to 3 months following last treatment. We will report on lesion recurrences among lesions treated with either regime 12 and 36 months after PDT. Cosmetic outcome will be determined by clinical assessment (visual inspection and palpation) 12 and 36 months after treatment. The results will be recorded on a 4-point ordinal scale as either excellent (absence of any stigmata other than scar formation after diagnostic punch biopsy), good (slight presence of fibrosis, atrophy or change of pigmentation), fair (moderate presence of fibrosis, atrophy or change of pigmentation) or poor (marked presence of fibrosis, atrophy or change of pigmentation).

The secondary endpoint will be to investigate relationship between clinical and pathological tumour characteristics and tumour recurrences rates, tumour thickness, histopathological BCC subtypes and immunohistochemical markers. Recurrence rate defined both as "raw" (total number of recurrences divided by the total number of tumours treated) and "strict recurrence rate" (total number of patients with recurrence divided by number of lesions observed for at least 36 month) will be reported.

Recurrence rate in relation to BCC subgroup analyses including clinical (superficial or nodular tumour), tumour size and histological characteristics will also be reported. BCC will on the basis of histological growth pattern be divided into two main types (aggressive or non-aggressive type). Tumours will additionally be studied with various immunohistochemical markers for expression of cell proliferation, invasiveness, vascularisation and growth factors.

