### **8.2 Statistical Analysis**

The statistical analysis is the responsibility of [name], Unit for applied clinical research, Faculty of Medicine, Norwegian University of Science and Technology (NTNU),

Clinical Study Protocol  
Version: Final revised  
Date: 2012-03-27

Sponsor: NTNU  
Study Code: NTNU 2011-1  
EudraCT No: 2011-004797-28 NO 20120327

Trondheim, Norway. Tabulation of summary statistics and data analyses will be performed using SPSS® software (PASW for Windows version 17.0 (PASW Inc)). The primary presentation and analysis will be based on data pooled across centres. Relevant summaries of data for individual centres, or combination of centres, for primary and secondary data (ie, patient characteristics, efficacy endpoints, and safety endpoints) will be made. Continuous data will be presented by descriptive statistics with the number of observations (n), mean, standard deviation, minimum, median, and maximum. Categorical data will be summarized in frequency tables using count and percentages. All tests will be carried out at a significance level of 5% without correction for multiple testing. All patients will be presented in separate data listings. Data from patients screened, but not included in the study, will not be presented in any tables or listings.

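### The protocol states its primary endpoint in four conflicting ways, the hypothesis names no time point and multiplicity correction is ruled out; only cure at 3 years was sized

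*Protocol*

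**What the plan says.** The protocol describes what is primary in four places:

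- **Section 8.2.2:** "lesion response rate determined by clinical assessment (visual inspection and palpation) 3, 12 and 36 months after" treatment. The hypothesis there sets regime 1 against regime 2 with a margin of 0.1. It defines the two parameters only as expected response rates, without a visit.
- **Section 3.1:** "The primary endpoint will be lesions cure rate and cosmetic outcome by treatment regime 1 compared to lesions cure rate by treatment regime 2". That comparison is set at 36 months. The same section then defines lesion response rate at 12 and 36 months.
- **Synopsis, Endpoints:** "The primary endpoint will be lesions response rate and cosmetic outcome determined by clinical assessment (visual inspection and palpation) 1 and 3 years after" treatment.
- **Section 8.2.1:** the primary outcome is cure or no cure "of a lesion at 3 years, i.e. a binary variable".

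The synopsis statistics paragraph adds a fifth outcome, not labelled primary: "logistic regression with lesion recurrence (yes/no, a binary variable) at 3 years will be employed". The sample size (synopsis and section 8.3) rests on the 3-year cure rate with a 10-point margin. On multiplicity, section 8.2 says "All tests will be carried out at a significance level of 5% without correction for multiple testing".

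**The concern.** The statements differ on the time point and on whether cosmetic outcome is primary. The one section that could settle the matter, 8.2.2, lists three visits and gives a hypothesis that fits any of them. Nothing says whether one visit is enough or all three are needed. With correction ruled out, the plan does not prevent a non-inferiority claim resting on whichever visit is favourable.

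Two things are at stake. One is a false-claim rate above the nominal level. The other, which is larger, is an early claim that hides a worse 3-year result: the timetable in section 3.8 puts the end of 1-year follow-up in Q4 2013 and of 3-year follow-up in Q4 2015, so an early primary result could be reported two years ahead.

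The modelled outcome in the synopsis raises a further question. A lesion that never cleared is not cured, but it has not recurred either.

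**Working it through.** **1. Which version was sized.** Inputs from section 8.3: cure 85% at 3 years, margin 10 points, 5% significance (sidedness not stated), 80% power, 170 lesions per group. Taking one-sided 5%, no true difference and independent lesions:

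n = (1.645 + 0.842)² × 2 × 0.85 × 0.15 / 0.10² = 158 per group.

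The Farrington-Manning score method gives 163. An exact unconditional score test has 81.3% power at 170, so 170 is consistent with exact software. Then 187 × 10/11 = 170 gives the allowance for loss. The figure therefore belongs to a single test of 3-year cure. No other visit and no cosmetic outcome was sized. (The 80% reference rate in the synopsis and section 8.2.1 against 85% in section 8.3, and the sidedness, are separate matters.)

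**2. False-claim rate if any one visit suffices.** The planned two-sided 95% interval means one-sided 2.5% per visit. With regime 1 exactly 10 points worse at all three visits, the chance of at least one false claim is 1 − P(Z₁, Z₂, Z₃ all < 1.96), with Z trivariate normal and common correlation ρ (assumed; the protocol gives none):

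| ρ | False-claim rate |
|---|---|
| 0.85 | 4.6% |
| 0.7 | 5.5% |
| 0.5 | 6.3% |
| 0 | 1 − 0.975³ = 7.3% |
| Upper bound | 3 × 2.5% = 7.5% |

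A simulation of 200,000 trials with nested responses and 170 lesions per arm agrees. Assumed control rates of 95/90/85% give 5.5%, and 92/86/80% give 5.3%, with regime 1 ten points lower throughout. For the synopsis version (12 and 36 months only) the figure is 3.9%. If each test were run at one-sided 5%, as the sample size implies, the three-visit figures would be 9.8% to 10.2%.

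**3. Early claim, late inferiority.** Assumed rates, regime 1 against regime 2: 93% v 95% at 3 months, 86% v 90% at 12 months, 75% v 85% at 36 months. At 3 months the standard error is √[(0.93 × 0.07 + 0.95 × 0.05)/170] = 0.0257, so the expected statistic is (−0.02 + 0.10)/0.0257 = 3.1, well above 1.96. In simulation the margin is met in 87% of trials at 3 months, 40% at 12 months and 2.6% at 36 months. Some visit succeeds in 87% of trials although regime 1 is 10 points worse at 3 years.

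**4. Recurrence against cure.** In arm k let u be the share of lesions never cleared and r the share that cleared and recurred. No cure is u + r; recurrence is r. Then:

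difference in no cure = (r₁ − r₂) + (u₁ − u₂).

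The two outcomes differ by u₁ − u₂. With 5% never cleared in both arms the shift is zero (if those lesions were dropped from the denominator, a 10-point difference in recurrence would read 10/0.95 = 10.5 points). A shift of 5 points, half the margin, needs 5% in one arm and none in the other. The protocol gives no figure for non-clearance by arm. The gap is real in this design: section 5.6.2 follows only lesions in complete response to 12 and 36 months, and sections 1.2 and 6.1 remove patients with persisting disease.

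**The case against.** The strongest defence is that the versions are fewer than they look. Sections 3.1 and 8.2.1 agree on 3-year cure apart from cosmesis, and the sample size and the synopsis model also point to 3 years. That stands, and it shows which endpoint was meant. It also leaves section 8.2.2, the operative testing section, as the one most out of line.

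The error rates depend on assumptions: the correlations, regime 1 at the margin at every visit, and success at any one visit being enough. If all three visits had to succeed, no adjustment would be needed. The protocol states neither rule.

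Four stronger readings are tempting and are not supported:

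- *Non-inferiority could be claimed on any of the listed outcomes.* Cosmetic outcome is a 4-point ordinal scale with no hypothesis or margin, so no such claim is defined for it and its contribution to error cannot be computed. Recurrence is a modelled variable and is never called primary. The open choice is among 3, 12 and 36 months of lesion response.
- *The 3-month comparison is unfair because regime 1 is judged before its re-treatment.* That follows only if the visit after the first session is the one used. Section 8.1 counts from the last treatment, and section 5.6.2 and the flow chart (visit 2b) give re-treated lesions a further 3-month visit. The text is ambiguous, not demonstrably unfair.
- *Each 5% of never-cleared lesions costs half the margin.* Only an imbalance between the arms does so. The last-observation rule for the ITT population would also carry a non-response forward if response were the outcome analysed, though it does not turn a non-response into a recurrence.
- *Any residual tumour seen before 36 months should count as failure.* Read literally, this would fail regime 1 lesions re-treated as planned. If, say, 20% were re-treated for residual tumour, regime 1 cure could not exceed 80%, against the 85% expected under conventional treatment in section 8.3, even if every re-treatment worked.

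**Conclusion.** Wrong as written. The current text contradicts itself on the time point and content of the primary endpoint, the hypothesis does not resolve it, and multiplicity correction is excluded. This is not detail that an analysis plan could fill in without overriding protocol text.

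The inflation is moderate: about 4.6% to 6.3%, at most 7.5%, instead of 2.5%, under the any-visit rule and with regime 1 at the margin throughout. The more serious risk is a claim from an early visit while 3-year cure is inferior; its size (87% against 2.6%) depends wholly on the assumed rates. The recurrence wording is a definite mismatch, but its effect equals the between-arm difference in non-clearance, which is unknown. All figures treat lesions as independent.

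**What to change.** - In the synopsis and sections 3.1, 6.1 and 8.2.2, name one primary endpoint, lesion cure at 36 months, and attach the 0.10-margin hypothesis to it, tested once.
- Define no cure as a lesion not cleared after completing its assigned regime (for regime 1, including the planned 3-month re-treatment), or recurring by 36 months. Planned re-treatment alone is then not failure.
- Make 3- and 12-month response and cosmetic outcome secondary.
- In the synopsis model, replace recurrence by cure or no cure.
- Reconcile section 5.6.2, section 8.1 and the flow chart on whether the 3-month assessment counts from the first or the last session.

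The cost is protocol wording, with no added lesions: a single primary test needs no adjustment. By contrast, keeping three visits primary with any one sufficient would, under Bonferroni, need (2.394 + 0.842)² × 0.255 / 0.01 ≈ 267 lesions per group at 85% and one-sided 2.5%, against 201 for a single test at that level. The downside is that early-response and cosmesis results become secondary.
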